### Gamma oscillation entrainment via electroencephalogram (EEG)

In this study, a 32-channel scalp EEG signal recording system (Brain Amp MR PLUS, Brain Products, Germany) with a sampling rate of 500 Hz will be utilized. The electrode positions will be based on the international 10/20 system, with CPz as the reference electrode and AFz as the ground electrode. Prior to the experiments, the impedance of all electrode channels will be adjusted to below 20 kΩ. Preprocessing of data from all subjects will be done using the Makoto pipeline and EEG Lab toolbox in MATLAB. We will assess gamma oscillation entrainment by calculating changes in power spectral density before, during, and after the intervention using custom MATLAB functions.

### RNA sequencing of the blood sample

Every participant will have a 1-mL blood sample taken from a vein by a trained nurse both at the start of the study and 2 weeks after the intervention period. This blood collection will allow us to assess changes in neuroinflammatory factors, nerve growth factors, and genes related to synaptic plasticity in the blood. Prior to the blood draw, participants will be advised to refrain from eating after 8 pm the previous day, as well as drinking and engaging in intense exercise. Breakfast will also be prohibited on the day of the blood draw. Once they have emptied their bladder, they will proceed to a laboratory room where a 1-mL venous blood sample will be collected into an EDTA anticoagulant tube. To this, 3 mL of TRIzol Reagent (LMAl Bio, China) will be added, ensuring thorough mixing. The mixture will then be incubated at 25 °C for 5 min and stored at − 80 °C. This rigorous process maintains the integrity and stability of the blood samples for subsequent biochemical analysis.

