**Discussion:**

This study will evaluate the safety and efficacy of gamma oscillations induced by 40-Hz visual-auditory stimulation in treating patients with upper extremity dysfunction after an acute cerebral stroke. Concurrently, we will explore potential mechanisms, including changes in synaptic-related genes and neural network connectivity. This trial is expected to provide evidence for the effectiveness of this new technique in treating upper extremity dysfunction after a stroke and improving patients’ quality of life.

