### Outcomes {12}

Pre-intervention (− t1), 2 weeks post-intervention retention (T2), 3 months (T3), and post-intervention 6 months follow-up (T4), cranial MRI scans (T1, T2, DWI, DTI, BOLD) and EEG will be employed to detect changes in neural network connectivity, Fugl-Meyer Assessment (FMA) and Brunnstrom Limb Function Recovery Scale will be used to assess motor function, transcranial magnetic stimulation (TMS) will be used to detect neurophysiological biomarkers including MEPs and CMCT, CT perfusion (CTP) will be employed to detect cerebral blood flow, and peripheral blood samples will be collected for RNA sequencing.

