### Plans for collection, laboratory evaluation and storage of biological specimens for genetic or molecular analysis in this trial/future use {33}

The blood sample of the participants will be collected by professional nurses. The samples will be mixed with Trizol solution at a ratio of 1:3 and stored in a − 80 ℃ freezer at the central laboratory of Shanghai Seventh People’s Hospital before sending to RNA sequencing.

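### The only blood assay named, RNA sequencing of whole blood lysed in TRIzol, measures pooled blood-cell transcripts; the article should not present it as circulating factors or as evidence of brain synaptic change

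*Protocol article*

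**What the plan says.** In the protocol article, the section on RNA sequencing of the blood sample states that the draws will allow the team to "assess changes in neuroinflammatory factors, nerve growth factors, and genes related to synaptic plasticity in the blood". Handling is described in two steps: "a 1-mL venous blood sample will be collected into an EDTA anticoagulant tube", and then "3 mL of TRIzol Reagent (LMAl Bio, China) will be added, ensuring thorough mixing". The section on biological specimens {33} agrees: "The samples will be mixed with Trizol solution at a ratio of 1:3", with frozen storage until the material goes to sequencing. Outcomes {12} gives the purpose of the blood: "peripheral blood samples will be collected for RNA sequencing". The RNA section times the draws "both at the start of the study and 2 weeks after the intervention period".

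The Methods paragraph of the abstract places alterations in synaptic-related genes among the secondary efficacy endpoints. The Discussion paragraph of the abstract says "we will explore potential mechanisms, including changes in synaptic-related genes and neural network connectivity".

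Statistical methods {20a}, headed as covering primary and secondary outcomes, gives a two-group t test, or a Wilcoxon test if the data are not normal, and names no covariate. It does not mention sequencing.

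**The concern.** What is measured and what it is said to show differ in two ways.

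First, the word factors, applied to inflammation and nerve growth, is normally read as released proteins. Sequencing reads RNA. A transcript level in blood cells is not the concentration of a protein in plasma.

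Second, the RNA in a whole-blood lysate comes essentially from blood cells. A gene labelled as related to synaptic plasticity may be expressed in those cells, but its level there does not observe a synapse. The background section {6a} cites the team's own mouse work for restored synaptic plasticity as the mechanism, and the abstract sets the genes beside brain network connectivity. A positive blood result could therefore be taken as human confirmation of a brain mechanism that this specimen cannot test.

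A further issue is which comparison is interpreted. Baseline blood comes from patients within one week of stroke onset, and the next draw follows the two-week intervention. A before/after change within one arm could reflect a changing mix of white cells and not altered expression in any cell.

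**Working it through.** **1. Specimen, assay and claim side by side**

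| Step | What the article gives | Where |
|---|---|---|
| Specimen | 1 mL EDTA venous blood; no plasma, serum or cell separation described | RNA sequencing section |
| Processing | 3 mL TRIzol added to the 1 mL, i.e. 1:3 | RNA sequencing section; specimens {33} |
| Assay | RNA sequencing; no other blood assay named | Outcomes {12}; specimens {33} |
| Said to assess | Inflammatory factors, growth factors, synaptic-plasticity genes | RNA sequencing section |
| Used as | Secondary efficacy endpoint; candidate mechanism | Abstract, Methods and Discussion |

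The two handling statements agree (1 mL : 3 mL = 1:3). The first three rows yield transcript levels pooled over blood cells. The last two claim more than that.

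**2. The plan's own figures**

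The article gives no figure for the gene endpoint. Its one design calculation, 28 per group for the Fugl-Meyer outcome, does reproduce (exact two-sided t test at effect size 0.995, alpha 0.05, power 0.95: 27.25, so 28), but has no bearing here.

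**3. Why a before/after change is fragile**

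A bulk transcript level is the sum over cell types of share × per-cell expression. Take two cell types and hold per-cell expression fixed. All shares below are assumptions, because the documents give no white-cell counts.

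Assume neutrophils go from 75% to 60% and lymphocytes from 25% to 40%, with r the lymphocyte-to-neutrophil expression ratio:

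apparent change = (0.60 + 0.40r)/(0.75 + 0.25r) − 1

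- r = 2: 1.40/1.25 − 1 = 12%
- r = 5: 2.60/2.00 − 1 = 30%
- r = 10: 4.60/3.25 − 1 = 42%

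The result depends heavily on the assumed shift. With g the granulocyte expression relative to the other white cells, the fold change is:

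| Granulocyte share | g = 0 | g = 0.2 | g = 0.5 | g = 1 |
|---|---|---|---|---|
| 80% to 60% | 2.00 | 1.44 | 1.17 | 1.00 |
| 75% to 65% | 1.40 | 1.20 | 1.08 | 1.00 |
| 70% to 65% | 1.17 | 1.09 | 1.04 | 1.00 |

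**4. What carries over to the randomised comparison**

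If the stroke itself shifts the mix by the same factor in both arms, the between-arm ratio at follow-up is unchanged: for example 1.30/1.30 = 1. In expectation, a shared shift adds noise and not bias. The figures in step 3 therefore apply to before/after readings within an arm.

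**The case against.** The best defence is that the article does not say what it is criticised for. The section is headed as RNA sequencing and places the genes in the blood, so factors can be read as their transcripts. No sentence equates blood transcripts with neuronal expression. The abstract only offers to explore mechanisms, and the main Discussion looks for neuroplasticity in circuits, connectivity and blood flow, not in blood genes. This stands as far as it goes: the over-reach lies in the word factors and in the endpoint and mechanism labels, not in an explicit claim to have sampled the brain.

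Three stronger readings are tempting, and the documents do not support them.

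- *Circulating proteins cannot be measured in this trial.* The consent section {26b} mentions about 2 ml of blood against 1 mL in the RNA section, and the latter closes by referring to later biochemical analysis. A condensed article may omit an assay. What can be said is that none other than sequencing is named.
- *The plan has chosen to ignore cell counts.* No sequencing model is described at all. Silence in an article about normalisation or covariates is not a decision, and such detail may sit in the full protocol or analysis plan.
- *The treatment comparison is biased by 12% to 42%.* Those are within-patient changes under assumed shares. Randomisation balances a stroke-driven shift in expectation. With 31 per arm, chance imbalance (for instance in infections) can still move the contrast, but that is true of any outcome.

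An objection to an obvious remedy also stands. Follow-up white-cell shares arise after randomisation, and the article itself cites immune effects of the stimulation. Adjusting for them could remove part of a real effect or bias the contrast.

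**Conclusion.** The point holds as one of labelling and inference. On the text, the named assay measures pooled blood-cell transcripts. It does not measure concentrations of inflammatory or growth-factor proteins and is not direct evidence of synaptic change in the brain, although the article's wording and its endpoint and mechanism labels invite both readings.

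No numerical error can be attached to the trial's result. The only quantities available are the assumed illustrations above: 1.00- to 2.00-fold apparent change within a patient, and none in expectation between arms from a shared shift. That the white-cell mix changes after acute stroke is general knowledge and not stated in the documents.

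The primary motor outcome, the sample size and the safety assessment are unaffected. What is at stake is what a secondary mechanistic result may be said to show.

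**What to change.** 1. Name the endpoint *peripheral blood transcript changes* wherever it appears, including the abstract.
2. State that factors means the transcripts of those factors. If protein concentrations were intended, the specimen and assay for them need to be named.
3. State that this result alone cannot support a claim about synaptic plasticity in the brain.
4. Base inference on the between-arm difference at follow-up, adjusted for each patient's baseline expression, in place of the unadjusted two-group test in {20a}. Do not draw conclusions from before/after change within an arm.
5. If cell mix is addressed, estimate the shares from the sequencing data and report the adjusted result only as a labelled sensitivity analysis, noting that follow-up shares are post-randomisation and may be affected by treatment.

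Items 1 to 3 are wording, as long as transcripts are what is meant. Item 4 uses the baseline draw already planned, and item 5 needs no extra blood. The article reports two patients included at the time of writing. The real cost is a more modest mechanistic claim.

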### Participant timeline {13}

Time schedule of enrolment, interventions, assessments, and visits for participants is shown in Table 1.

### Sample size {14}

The sample size calculation was conducted using G*power software (v3.1.9.2). The effect size of this study was estimated from a study conducted by Kaux et al. [29] who investigated the effects of transcranial direct current stimulation associated with physical therapy in acute stroke patients evaluated by the upper extremity section of the Fugl-Meyer Test, which was determined to be 0.995. The experiment employs a 1:1 simple randomization, n1 = n2. According to a prior difference between two independent means analysis *t* test, with a power of 0.95 and an error probability of 0.05, we applied these values to compute a sample size of *n* = 28. Accounting for a 10% attrition rate, we determined that each group should comprise 31 participants, yielding a total of 62 stroke patients included in the study. It is important to note that all enrolled patients received clinical medications and conventional rehabilitation treatments that were generally uniform.

### Recruitment {15}

The project is based at the Department of Neurology and Neurorehabilitation of the Seventh People’s Hospital affiliated with Shanghai University of Traditional Chinese Medicine. This hospital is a national comprehensive stroke and a member of the national neurology clinical research centre. It possesses outstanding capabilities in acute stroke management and post-stroke functional rehabilitation. Over the past 3 years, it has treated more than 1000 cases of stroke, guaranteeing the enrolment of participants.

## Assignment of interventions: allocation

### Sequence generation {16a}

Participants will be allocated by simple randomization. The random number will be generated by SPSS version 20.0 for Windows (IBM Co., Armonk, NY, USA). The participants will be sample randomized into one of the two treatment groups (40-Hz stimulation vs. random frequency stimulation) in a 1:1 ratio after baseline evaluation.

### Concealment mechanism {16b}

The randomization code generated by the computer will be sealed in an opaque, sealed envelope and is only available to the physician who performs the intervention and not involved in the outcome evaluations or patient follow-ups. Member responsible for patient enrollment, outcome evaluation, and follow-up are blind to the allocation sequence.

### Implementation {16c}

The primary investigators will be responsible for enrollment of participants. The enrolled patients will be assigned to interventions according to the computer-generated random numbers.

## Assignment of interventions: blinding

### Who will be blinded {17a}

Procedures will be implemented to control for expectancy effects related to visual-auditory stimulation. Persons who will be masked to visual-auditory stimulation status (40-Hz stimulation vs. random frequency stimulation) are participants, authorized representative of the patient (if applicable), personnel involved in outcome assessments, follow-up, data collection, and analysis. Unmasked personnel will be the engineers who set up the stimulation protocol for the device and physicians who perform the intervention.

### Procedure for unblinding if needed {17b}

We do not anticipate any requirement for unblinding unless it is relevant to the participant safety.

## Data collection and management

### Plans for assessment and collection of outcomes {18a}

The physician who performed the intervention is qualified and adequately trained about visual-auditory stimulation, and he has performed the intervention more than 50 patients. All outcomes will be evaluated by two experienced neurologists who are blind to the grouping of the patients. All imaging examinations will be completed in the same machine.

### Plans to promote participant retention and complete follow-up {18b}

We will make every effort to lower the obstacles to attending study visits, including offering the participants to come at preferred times and offering remote options for non-face-to-face study tasks via videochat.

### Data management {19}

Each patient’s ID and baseline information will be collected. Collected data will be recorded on paper case report forms (CRFs), then entered into electronic data capture (EDC) system and uploaded to a central server. Data integrity will be enforced through appropriate range checks and consistency checks at the time of data entry, before the data are committed to the database. Data entered into the database will be retrievable for viewing through the data entry application. A complete back up of the primary database will be performed once a week and stored indefinitely on a twin server. The CRFs and EDC will be kept for at least 5 years after publication in case of any inquiry. Personal information about the enrolled participants will be safely and confidentially kept. After completion of the study, the CRFs and all the data collected will be stored anonymously in the password-protected central server and restricted to relevant members of the research team. Paper copies of the CRFs will be stored in a locked cabinet in the relevant research office.

### Confidentiality {27}

Personal information about the enrolled participants will be safely and confidentially kept. After completion of the study, the CRFs and all the data collected will be stored anonymously in the password-protected central server and restricted to relevant members of the research team. Paper copies of the CRFs will be stored in a locked cabinet in the relevant research office.

### Plans for collection, laboratory evaluation and storage of biological specimens for genetic or molecular analysis in this trial/future use {33}

The blood sample of the participants will be collected by professional nurses. The samples will be mixed with Trizol solution at a ratio of 1:3 and stored in a − 80 ℃ freezer at the central laboratory of Shanghai Seventh People’s Hospital before sending to RNA sequencing.

## Statistical methods

### Statistical methods for primary and secondary outcomes {20a}

Statistical analysis was conducted using GraphPad Prism version 8.0 and MATLAB 2021a. For continuous variables, the normality of the data distribution in all datasets was assessed using the Kolmogorov–Smirnov test. Continuous variables were presented as mean ± standard deviation (SD) with range values for normally distributed data, or as the medians with the interquartile ranges (IQRs) for non-normally distributed data, respectively. Categorical variables were presented as frequencies and percentages. If the data followed a normal distribution, the difference between the two groups was assessed using Student’s *t* test. If the data did not follow a normal distribution, the Wilcoxon rank test was employed. For categorical variables, a chi-squared test or Fisher’s exact test was utilized for comparison. A significance level of *P* < 0.05 was considered statistically significant.

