**Methods:**

This trial is a prospective, randomized controlled, double-blind study. All enrolled patients were randomly assigned to two groups. The experimental group received intervention through 40-Hz visual-auditory stimulation, while the control group underwent intervention with randomly matched visual-auditory stimulation frequencies. The primary efficacy endpoint is the change in motor function. Secondary efficacy endpoints include motor-evoked potentials, cerebral hemodynamic changes, neural network connectivity, and alterations in synaptic-related genes. Safety evaluation included major adverse events, all-cause mortality, and photosensitive epilepsy. Assessments will be conducted at baseline, after a 14-day treatment period, and during subsequent follow-up visits (at 3 and 6 months) post-treatment. The differences between the two groups will be compared.

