## Primary outcomes

### Fugl-Meyer Assessment (FMA)

Motor function recovery will be assessed using the Fugl-Meyer Assessment (FMA). The FMA rates each sub-item on a scale of 3, with scores of 0 (unable to complete), 1 (partially completed), and 2 (fully completed). The upper limb motor assessment comprises a total of 33 items, with a maximum score of 66.

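### The FMA comparison is not adjusted for baseline FMA, a normality pre-test picks the test, and change or follow-up score is left open; one prespecified ANCOVA would be a free improvement

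*Protocol article*

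**What the plan says.** The article's section on statistical methods for primary and secondary outcomes {20a} sets a two-step rule for continuous variables. First, "the normality of the data distribution in all datasets was assessed using the Kolmogorov–Smirnov test". Then "If the data followed a normal distribution, the difference between the two groups was assessed using Student’s *t* test"; otherwise, "If the data did not follow a normal distribution, the Wilcoxon rank test was employed". No covariate is named. The section on additional analyses {20b} adds no adjusted analysis.

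The abstract's Methods paragraph says "The primary efficacy endpoint is the change in motor function". Section {20a} does not say whether the test is run on that change or on the score at follow-up.

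FMA is assessed pre-intervention (Outcomes {12}), and patients are randomised "in a 1:1 ratio after baseline evaluation", so the baseline score is in hand at allocation. The scale is bounded: "The upper limb motor assessment comprises a total of 33 items, with a maximum score of 66". Sequence generation {16a} states "Participants will be allocated by simple randomization", and the sample size section {14} says "The experiment employs a 1:1 simple randomization, n1 = n2".

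**The concern.** Eligibility admits Brunnstrom levels I to IV, so initial arm function will vary widely, and baseline FMA can be expected to predict later FMA. A comparison that leaves it out as a covariate gives up precision the trial has already paid for. It also lets a chance difference in initial severity pass into the estimate.

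Two matters are left for the data or the analyst to settle. The Kolmogorov–Smirnov result decides whether the trial reports a difference in means or a shift in ranks, and the answer could differ from one visit to the next. The choice between change and follow-up scores is not written down, yet it affects power more than most other choices in the analysis.

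**Working it through.** **Inputs from the article (Sample size {14}).** Effect size d = 0.995, alpha 0.05, power 0.95, 1:1 allocation, n = 28 per group before attrition, 31 per group (62 in total) after it.

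**Inputs assumed.** The baseline-to-follow-up correlation r of FMA is not in the article; r = 0.6 to 0.8 is used. A true difference of 0.6 SD, smaller than planned, is used as an example. SDs are taken as equal at both visits.

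**1. The plan's own figure.** Two-sample t test, noncentral t, two-sided: 28 per group gives power 0.955 and 27 gives 0.948. The stated 28 reproduces.

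**2. Variance of the treatment effect**, relative to a follow-up-only comparison: change score 2(1 − r), ANCOVA 1 − r². ANCOVA relative to change is therefore (1 − r²) / [2(1 − r)] = (1 + r)/2.

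| r | change / follow-up | ANCOVA / follow-up | ANCOVA / change |
|---|---|---|---|
| 0.6 | 0.80 | 0.64 | 0.80 |
| 0.7 | 0.60 | 0.51 | 0.85 |
| 0.8 | 0.40 | 0.36 | 0.90 |

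ANCOVA saves 36–64% against follow-up scores and 10–20% against change scores. Below r = 0.5 a change score is worse than the follow-up score alone (at r = 0.3 its variance ratio is 1.40), while ANCOVA is still better (0.91).

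**3. Power at 28 per arm, r = 0.7.** The difference is divided by the square root of the variance ratio.

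| True difference | Follow-up t | Change t | ANCOVA |
|---|---|---|---|
| 0.6 SD | d = 0.600: 0.60 | 0.6/√0.60 = 0.775: 0.81 | 0.6/√0.51 = 0.840: 0.87 |
| 0.995 SD (as planned) | 0.955 | 0.997 | 0.999 |

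**4. Chance imbalance at baseline.** With 31 per arm the standard error of the baseline difference is √(2/31) = 0.254 SD, so a gap of 0.5 SD or more arises in about 5% of trials. Given a 0.5 SD gap, r = 0.7 and no treatment effect:
- The follow-up difference is shifted by 0.7 × 0.5 = 0.35 SD.
- The change difference is shifted by (0.7 − 1) × 0.5 = −0.15 SD.
- ANCOVA removes the shift under a linear relation.

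At 28 per arm the follow-up test needs a difference of 2.005 × √(2/28) = 0.536 SD, and the conditional SD is √(2/28 × 0.51) = 0.191. The conditional type I error is then about 0.17. For the change score the critical value is 0.536 × √0.60 = 0.415, and the conditional error is about 0.08.

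**5. The pre-test.** The two-stage rule was simulated with 28 per arm, 4,000 runs per scenario and the Kolmogorov–Smirnov test with estimated parameters applied in each arm. Overall type I error was 0.047–0.054 for normal, bounded and exponential data. Both arms passed as normal in 91% of normal, 80% of mildly bounded, 26% of skewed bounded and 7% of exponential trials. Error is controlled; which effect measure is reported depends on the data.

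**The case against.** The strongest reply is that nothing here is invalid. Randomisation justifies the unadjusted test. Its 5% error rate already averages over chance baseline gaps, and the conditional figures above describe only the unlucky trials. The pre-test rule is stated in advance and showed no error inflation. At the planned effect the trial has power 0.955 as it stands. All of this is correct, and it is why the point is an improvement and not an error.

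A reader might infer four stronger things that the article does not support.

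- **That baseline function is not used at all.** The abstract defines the endpoint as a change, and a change score uses baseline. Against that reading ANCOVA takes power from 0.81 to 0.87 in the example, not from 0.60 to 0.87.
- **That Brunnstrom stage is to be analysed by a t test.** Section {20a} offers the t test for continuous variables and chi-squared or Fisher's exact test for categorical ones. It does not say which class the stage falls in.
- **That simple randomisation undermines the sample size.** An exact 31:31 split has only about a 10% chance, so the equality in section {14} is best read as the ratio assumed in the calculation. Uneven arms cost very little: at d = 0.995, power is 0.971 for 31:31, 0.969 for 27:35 and 0.964 for 24:38.
- **That allocation must be stratified.** Simple randomisation is valid. Inclusion has begun (Trial status), so changing the method now is a protocol amendment with its own trade-offs.

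What the reply does not answer is that section {20a} leaves the analysed score open, lets the data choose the effect measure, and omits a covariate that is already collected.

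**Conclusion.** The point holds as a recommendation on efficiency and prespecification. The stated test is valid and the stated sample size is right for it. The gain depends on which score was intended, which the article does not settle: 36–64% of the variance if follow-up scores are tested and 10–20% if change scores are, for r between 0.6 and 0.8. In the 0.6 SD example at r = 0.7 this is 27 or 6 percentage points of power. If the true effect is as large as planned, the gain in power is small under either reading. The correlation and the 0.6 SD difference are assumptions; the article gives neither. Protection against chance baseline imbalance and a single effect measure fixed in advance are gained in either case.

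**What to change.** In section {20a}, replace the pre-tested choice between t and Wilcoxon for FMA by one prespecified analysis: ANCOVA of follow-up FMA with treatment group and baseline FMA as terms and robust standard errors, reported as an adjusted mean difference with its confidence interval, with no normality pre-test. This also settles the question of change or follow-up, because ANCOVA estimates the same treatment effect for either score when baseline is in the model. Analyse Brunnstrom stage as an ordinal outcome adjusted for baseline stage, for example by a proportional-odds model.

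The cost is a change of wording, best made before any unblinded data are seen. No extra measurement or patient is needed, and the sample size can stay as it is. Blocked or stratified allocation for the patients still to be randomised is optional: it would need a new list, new envelopes and an amendment, and it is not part of this fix.

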### Functional connectivity by magnetic resonance imaging (MRI)

We will use a 3-T MRI scanner (Siemens Skyra, Erlangen, Germany), along with a circular surface coil to investigate changes in the brain. This will include evaluations of gray matter density, cortical thickness, subcortical nuclei volumes, and functional connectivity. Each participant will undergo an MRI scan lasting approximately 25 min. During the scan, they will have their eyes closed and extra padding will be placed around their ears to reduce noise interference. We will analyze changes in neural network connectivity using human connectomics. By integrating intelligent imaging technology with multimodal imaging data, including T1, DTI, and BOLD functional MRI, we can compare alterations in brain fiber connectivity patterns and changes in brain functional regions before and after treatment. This approach allows us to visualize and quantify functional connections between brain regions, alterations in the number of nerve fiber bundles, changes in the direction of nerve fiber bundle pathways, and changes in the volume of functionally abnormal regions.

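### The only significance rule, P < 0.05 with no adjustment stated, also covers RNA-sequencing genes and connectome connections, so about 5% of null tests there would be declared significant

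*Protocol article*

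**What the plan says.** The statistical methods section (item 20a) is headed for both primary and secondary outcomes. It prescribes a normality check, then a t test or a Wilcoxon test for continuous variables and a chi-squared or Fisher test for categorical ones. It closes with a single threshold: a P value below "0.05 was considered statistically significant". It names no adjustment and exempts no outcome.

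The Methods part of the Abstract defines what falls under that heading: "Secondary efficacy endpoints include motor-evoked potentials, cerebral hemodynamic changes, neural network connectivity, and alterations in synaptic-related genes". Two of these are high-dimensional by their method of measurement:

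- The section on RNA sequencing of the blood sample says that the samples will be used to "assess changes in neuroinflammatory factors, nerve growth factors, and genes related to synaptic plasticity in the blood". It gives three classes of gene but no list.
- The MRI section uses connectomics to "visualize and quantify functional connections between brain regions", alongside some summary measures. It names no specific connection and no number of regions.

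On the purpose of these measurements, the Discussion part of the Abstract says "we will explore potential mechanisms, including changes in synaptic-related genes and neural network connectivity". The section on additional analyses (item 20b) offers no separate analysis of genes or connections.

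**The concern.** A threshold of 0.05 per test is ordinary for one outcome. It serves poorly as the decision rule for a family of tens to thousands of parallel tests, because the number of null results called significant grows in proportion to the number of tests. The section does set a rule for secondary outcomes, and two of those outcomes are such families, so this is more than a missing detail: the rule as published gives a poor result when followed.

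At stake is the part of the objective that concerns mechanism. If some genes or connections reach P < 0.05 whether or not the stimulation does anything, a list of significant synaptic genes or altered connections says little about whether gamma stimulation changed them.

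**Working it through.** **Inputs from the document.** Threshold 0.05 per test, no adjustment stated (item 20a). Genes and connectivity are secondary efficacy endpoints (Abstract, Methods). Group size is 28 analysed per arm (Sample size, item 14).

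**Input not in the document.** The number of tests, m. Every value of m below is an assumption.

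**The plan's own figure.** The only computed figure is the sample size. A two-sided t test with standardised effect 0.995, alpha 0.05 and power 0.95 needs 27.25 per group, so 28, as stated. That figure concerns the Fugl-Meyer score and does not depend on this point. It is used here only as the group size for the simulation.

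**Expected chance hits.** If all m tests are null and each has its nominal size, the expected number significant is 0.05 × m. This holds whatever the correlation between tests; correlation changes the spread only. The chance of at least one hit is 1 − 0.95^m, which does assume independence. For R regions, the number of connections is R(R − 1)/2.

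| Assumed family | m | 0.05 × m | P(at least one), if independent |
|---|---|---|---|
| Very short list | 20 | 1 | 0.64 |
| Targeted genes | 50 | 2.5 | 0.923 |
| Targeted genes | 100 | 5 | 0.994 |
| Targeted genes | 200 | 10 | 0.99996 |
| Connections, 100 regions: 100 × 99/2 | 4,950 | about 248 | about 1 |
| Transcriptome-wide | 10,000 to 20,000 | 500 to 1,000 | about 1 |
| Connections, 360 regions: 360 × 359/2 | 64,620 | 3,231 | about 1 |

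The last two rows apply only if testing is transcriptome-wide or uses a fine parcellation. The document states neither.

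**When some effects are real.** Simulation with 28 per arm, independent tests, and true effects of 0.8 standard deviations where present (the effect size and the share of true effects are assumptions). Figures are mean counts.

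| m (true effects) | Flat rule: hits, of which false | Benjamini-Hochberg 5%: hits, of which false |
|---|---|---|
| 50 (5) | 6.3, of which 2.1 (34%) | 2.5, of which 0.2 |
| 200 (20) | 25.7, of which 8.9 (35%) | 9.1, of which 0.5 |
| 15,000 (150) | 866, of which 740 (85%) | 17, of which 1.1 |

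**Price of the correction.** True effects found are hits minus false hits. With 50 genes they fall from 6.34 − 2.15 = 4.19 to 2.46 − 0.18 = 2.28 of 5. With 200 genes they fall from 25.71 − 8.94 = 16.77 to 9.07 − 0.48 = 8.59 of 20.

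**The case against.** The strongest reply is that this is an omission. The section is generic, never mentions genes or connections, and does not say that its P values are unadjusted. A level of 0.05 could be applied to adjusted values. Some outcome-specific methods stand elsewhere, such as the MEP summaries and the EEG pipeline, and a full protocol or analysis plan that is not shown may well contain false discovery control. That possibility limits the point to the rule as published. It does not remove it: the section covers secondary outcomes by its heading, attaches plain two-group tests to a single threshold, and makes no exception. If an adjusted rule exists elsewhere, this text needs to be aligned with it.

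The second reply is that the number of tests is unknown, and this stands in full. The gene classes are targeted, and the MRI section also lists summary measures such as region volumes. A reader might infer that thousands of false genes or connections are to be expected. The document does not support that, because it states neither transcriptome-wide testing nor any number of regions.

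The third reply is that the work is framed as exploring mechanisms, which also stands and reduces the harm. A reader might infer that the trial sets out to prove a mechanism and is near certain to find one. The stated aim is to explore, and near certainty would need both an assumed number of tests and independence, whereas co-expressed genes and connections that share regions are correlated. Nor should the count be multiplied freely over visits: the RNA section draws blood at the start and 2 weeks after the intervention period, although the Outcomes section reads as if blood were taken at every assessment.

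**Conclusion.** The concern holds, limited to the gene and connection outcomes. As published, the only significance rule would declare about 5% of null genes or connections significant. With an assumed 50 to 200 null genes that is 2.5 to 10 expected chance hits, and with an assumed 100 regions about 248 connections. These expectations rest on the assumed number of tests and on each test having its nominal size, but not on independence. If only some 20 tests were run, one chance hit would be expected and the matter would be minor, but no such short list is stated.

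A reader might infer that the trial's main conclusion is compromised. It is not: the two primary outcomes, the Fugl-Meyer and Brunnstrom scales, and the sample size do not depend on this rule for genes and connections. The exploratory framing lowers the stakes further. The point remains worth correcting because these outcomes are listed as secondary efficacy endpoints, to which the threshold applies.

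**What to change.** Amend the statistical methods section (item 20a) along these lines:

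> The threshold P < 0.05 applies to outcomes that are single scalar measures. Gene-wise and connection-wise group comparisons are declared by the Benjamini-Hochberg procedure at a false discovery rate of 5% within each family (genes; connections). For connections, a network-based permutation test may be specified instead. Genes and connections that reach only nominal P < 0.05 are reported as exploratory.

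Each family should be defined, and one method for connections chosen, before the comparative data are seen.

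The cost is a few sentences and a standard routine in MATLAB, which the section already names. The downside is fewer genes and connections declared significant. In the simulated targeted sets, roughly half of the true effects found by the flat rule were no longer declared (4.19 to 2.28 of 5; 16.77 to 8.59 of 20). Neither the sample size nor data collection changes.
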